### Relevance of the DCE

A targeted literature research on acceptance models was conducted to analyze acceptance dimensions and criteria that impact individual’s acceptance. Criteria from different perspectives, such as those of the patients, system, and provider, were analyzed to investigate the concept of acceptance with respect to the value of digital interventions. Acceptance refers to the willingness of individuals to engage in a health intervention or health service [34]. Technology acceptance models provide information on variables that influence acceptance, such as perceived usefulness, perceived ease of use, subjective norms, or user experience [35-37]. Extensions of the models explain the interrelationships between the beneficial influencing factors and the burdensome influencing factors as a balancing process [38]. However, the models are limited in evidence regarding specific attributes that represent a benefit or a cost or burden to individuals or, specifically, patients. No information is provided on how impactful individual aspects of digital information are. HPR studies were conducted to generate evidence regarding the weighting of attributes. Thus, the presented DCE was developed.

The aspects of digital technologies (eg, data processing) have already been examined in various studies. There are studies that focus on digital apps on mobile devices [39,40]. Among these studies, attention is partly focused on data processing only [41,42]. Other studies examine factors of communication (eg, information giving, information transfer, and contact) [41-43]. Most of the studies do not include health-related goal variables [39,44]. Thus, there is a gap in holistic evidence on preference research on digital interventions. This study aims to generate evidence for all possible digital technologies (not only digital apps).

### Development of Attributes and Levels

Different digital technologies have been investigated in different studies in the context of therapies and were therefore considered in the prestudy (robots, voice assistants, digital health apps, digital health devices, etc). As digital technologies have an unlimited set of attributes, limitations arise from the fact that decision makers cannot consider all possible attributes in their evaluation [18]. In a DCE, alternatives are described by decision-relevant criteria that are identified from the set of possible attributes [18].

A targeted literature search was conducted to identify the characteristics of health-related interventions in the context of the digital transformation associated with the use of digital technologies. First, digital transformation in health care was considered. Digital transformation became essential due to the rapidly changing and increasing needs and expectations in health care [45-47]. Digital technologies are innovations to achieve certain goals of digital transformation: flexibility of place and time, flexibility of the range of care, expansion of access for patients considering gains and pains, improvement of health literacy, participation and personal responsibility of patients, and improvement of information structures [11,48]. Certain characteristics (attributes) of digital technologies are necessary to achieve these goals. In total, 17 attributes were identified in the literature: communication, emergency communication, contact with professionals, distance to technology, emotions, speech, participation, recognition, feedback, data security, pick-up and drop-off function, entertainment, usefulness, place, location dependency, duration, and frequency.

Formative qualitative research is foundational to the development process of HPR studies [49]. Therefore, we conducted semistructured pilot interviews with patients with stroke (n=14) and experts in neurorehabilitation (n=5) to identify and cluster the decision-relevant criteria from the subset of 17 attributes. Patients were asked to describe their physical and daily living limitations owing to the diagnosis and their experiences with neurorehabilitation. The patients were also asked about their attitude, opinions, and expectations regarding digital technologies. After the humanoid assistance robot “Pepper” was presented, the participants were asked about their attitude toward the robot. Attributes defined from the literature were presented with descriptions on cards. The patients were asked to rank the attributes according to their relevance. Furthermore, the patients described what they thought a future therapy might look like by using a different card of attributes. An interview guide was used for this process. We used semistructured interviews, which allow an open discussion style and an interview to be individualized, allow spontaneous in-depth discussion of interesting statements, and allow a return to relevant key questions [50]. Experts estimated the patients’ point of view regarding the questions asked according to their experience. A list of seven decision-relevant criteria was developed: (1) explanation and presentation of exercises, (2) information from digital technologies, (3) contact with professionals, (4) patients’ choice in the therapy process, (5) data processing, (6) copayment per month, and (7) therapy success within 6 months. Thus, the list included 5 attributes that are technical aspects (attributes 1-5). In addition, copayment per month and therapy success within 6 months complete the decision context. Therapy success refers to an individual’s goal attainment. Goal attainment is determined by the improvement in body function, which in turn leads to a resumption of activities of daily living. The full list was concretized through discussion rounds, such as focus groups and workshops with experts in health care. The final list was transformed into a decision model.

### Descriptive Framework

Preference evidence can be identified by observing human behaviors using elicitation tasks. In a preference elicitation task, participants evaluate assigned alternatives or objects according to their preferences. In this study, we determined that the preference elicitation task would lead to the goal of determining a patient’s willingness to accept the trade-offs between the characteristics of therapy using digital technologies. The descriptive framework was created to contain all decision-relevant attributes, levels, and descriptions of the decision context that will be used to communicate the content of the elicitation tasks (Table 1).

**Table 1 table1:** Descriptive framework.

Attributes	Description	Level 1	Level 2	Level 3	Level 4	Level 5
Explanation and presentation of therapy exercises	Patients receive information, instructions, and assistance on how to perform the exercises, with an explanation and presentation of therapy exercises.	Sounds and speech	Descriptive texts	Images	Videos	Spatial movement
Information in therapy	Patients receive information from the digital support system in digital therapies, but there are also digital therapies where patients do not get any information.	No information	Therapy and rehabilitation process	Diagnosed disease	Patient’s current health status	Change in health status owing to therapy
Contact with health care professionals	Patients have contact with health care professionals in a digital therapy, but there are also digital therapies in which patients have no contact with professionals.	No contact	Contact is indirect (messages)	Contact is direct (telephone or video)	—^a^	—
Patients’ choice in the therapy process	Patients have certain choices in a digital therapy. Therefore, patients have an influence on the design of therapy processes, but there are also therapies where patients have no influence.	No influence	Selection of therapy exercise with a certain degree of severity	Pace of therapy exercise	Time of therapy (frequency, duration, and start)	Place of therapy (eg, home, clinic, or practice)
Data processing	There is data processing in digital therapies. Data about patients are collected and forwarded, but there are also digital therapies where no data are processed.	No data processing	Processing of data about the person	Processing of data about the diagnosis	Processing of data about the progress of the therapy	—
Copayment per month	Patients in digital therapies contribute to the cost of the therapy with a copayment per month. There are also digital therapies where patients have no copayment.	€80 per month	€60 per month	€40 per month	€20 per month	No copayment
Therapy success within 6 months	Patients have success in a digital therapy by achieving their therapy goals. Therapy goals are set at the beginning of a therapy, but not all patients achieve their goals within 6 months.	60 out of 100 patients	70 out of 100 patients	80 out of 100 patients	90 out of 100 patients	100 out of 100 patients

^a^The number of levels of each attribute is not necessarily equal, so the number varies between 3 and 5 levels. Therefore, for the attributes contact with health care professionals, no data are available for levels 4 and 5, and for the attribute data processing, no data are available for level 5. Furthermore, the respondents in the study were recruited in Germany. Accordingly, the data on the copayment per month were given in euros (€) and not in US $ (€0.92=US $1). For visual representations of each level, see Multimedia Appendix 1.

### Choice Context

In choice experiments, participants are asked to assume that their therapy decision is made in the context of a specific or their current health condition. Our study sample included both therapy-experienced and therapy-inexperienced participants. Therefore, the participants are asked to assume a health condition that requires rehabilitative therapy.

### Elicitation Tasks

The challenge in a DCE is to dissolve the response uncertainty and to trace the preference information back to the individual attributes through repeated choice tasks, with participants “forced” to make a decision between digital therapies. For the professional group, there was no choice available within the choice task. The underlying choice task is a ranking task, which follows a fixed procedure. The choice starts with the selection of the best alternative among 3 choices. The choice is iterated with the remaining 2 so that a complete ranking is achieved. Thus, the DCE uses a best-best choice format [51].

Participants’ willingness to choose the digital therapy was determined by the following follow-up question: “Would you really choose the previously selected digital therapy in real life to improve your health?” Recently, the dual response “none” has been established as a variant in choice experiments [52,53]. A dual response of “none” asks for 2 responses for each task: one choice between the available product alternatives and one between the “none” concept and the previous alternatives. Essentially, it is a choice between the most preferred alternative and none. If participants would actually buy or take the alternative, they would not prefer none, but if they would not buy or take the alternative, they would prefer none to the given alternative [54]. The dual response “none” design takes more time to answer and is an increase in analysis effort owing to a complex design. However, more information is generated, which makes the design more efficient and powerful. Estimation errors are reduced, and the underlying model estimate is not significantly changed [52]. This design provides a higher resolution for individual-level preferences. As there is less “missing” information when participants select “none” as their preferred alternative, more information is available for individual-level modeling [54]. The final survey instrument comprised 6 choice tasks. The number of choice tasks was determined by the underlying experimental design, possible number of participants, and information received per task. No names, brands, or companies were named in the presentation of the choice tasks; therefore, the tasks were unlabeled. In addition, unlabeled alternatives were preferred because the study objectives were to estimate the marginal rates of substitution and value equivalents for therapy attributes [18].

### Elicitation Format

Participants will be familiarized with the attributes and expressions through descriptions and explanations before the first task. In addition, participants will see a tutorial and exercises to answer the choice tasks. Participants will answer a choice task with a clearly dominant alternative (copayment=none; treatment success=100%) so that an understanding of how to answer the DCE is tested.

### Experimental Design

Proper design and implementation of the DCE requires the consideration of the choice context, composition of choice sets, and framing of choice questions and instructions [55]. The results of the preliminary study indicated lower attention and concentration abilities in the experimental group. This finding, along with the evaluation of participants, led to the decision to use a partial design (choice tasks include 4 of the 7 attributes) [18,56]. Experimental design software was used in this study (Sawtooth Software Inc; ChoiceMetrics).

The underlying experimental design is a fractional-factorial efficient Bayesian design (D-error) to maximize the ability to identify participant preferences and variability in preferences across participants [56].

The experimental design was based on the following assumptions: minimal overlap, level balance and orthogonality. *Minimal overlap* means that each level is shown as few times as possible in a task. If the number of levels of an attribute is equal to the number of concepts in a task, each level is shown exactly once. Assumptions also were *level balance* which means that each level of an attribute is shown approximately the same number of times. *Orthogonality* means that levels are chosen independent of other levels so that the benefit of each level can be measured independent of all other effects).

Owing to the complexity of the experimental design in terms of the size of the decision model (7 attributes and 3-5 levels), the experiment was blocked. Combinations of alternatives are drawn from the total selection in 20 blocks in such a way that each level is combined as often and as evenly as possible. The study will analyze both the main and interaction effects. By combining all possible levels with each other (2-way frequency), sufficient information is generated to be able to measure the interaction effects. The allocation of the blockers is randomized. When a survey is stopped and choice tasks are not completed, they are made available to other participants so that all choice tasks are provided.

### Survey Instrument Design

Designing an effective survey instrument requires numerous connected decisions that are built on the decision context, attribute selection, and experimental design. The DCE requires a survey instrument that (1) explains to participants the various aspects of digital technologies that may differ across therapy options and (2) asks participants to indicate their preference for therapy options as aspects change. The final instrument is web based and self-completed by the participants.

The information presented to participants was developed by preparing descriptions for each attribute and level. Patients with stroke often experience cognitive impairment. Therefore, special attention must be paid to the layout of the survey. The design of the survey and the potential layout of the choice task should include the appropriate use of text and icons. An appropriate and well-designed layout can minimize the cognitive efforts required to compare alternatives and evaluate trade-offs. Because of the visual perceptual deficits in patients with stroke, icons should have good color contrast, clearly delineated lines, and a monochromatic design. We assessed the clarity and completeness of the DCE survey instrument and tested different choice formats (selection from 2 or 3 alternatives, best vs best-worst selection, and full vs partial design).

We limited the time required to complete the survey to a maximum of 30 minutes to minimize dropouts and to reduce data quality toward the end of the survey. First, we administered the quantitative survey with the final survey design in the control group. A pilot test was conducted, and the data collection was stopped after 150 completed questionnaires in the control group. Preference data were tested using a conditional logistic regression model to check for appearance validity, assumed signs and coefficients, and estimation problems.

We planned 3 sections for the web-based questionnaire: a study description and introduction to the attributes, the DCE, and the question section on sociodemographic and therapy and technology experience. The content of the survey will be clarified through an introductory description of the DCE survey technique at the beginning of the questionnaire. Here, participants will learn that they will be presented with hypothetical therapy alternatives in various combinations and that each alternative is described by 7 attributes. The questionnaire is expanded with questions on sociodemographic factors (including for inclusion and exclusion), sociocultural background, therapy-related and technology-related experiences, and health and quality-of-life assessment [57]. The questionnaire also includes a questionnaire assessment and questions on digital health literacy [58]. Different questions are designed to analyze the cognitive and perceptual limitations of the experimental group (Textbox 1). Metadata (or paradata) will provide information about the content of the health preference data. These data include the time taken to complete the survey and each question as well as information on dropout rates. The coding software used was Survey Engine GmbH. Textbox 1 presents the structure and content of the survey questionnaire.

Structure and content of the survey questionnaire.

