### Research Questions and Study Aim

This ongoing study will address the following question: Which criteria of digital technologies impact patient and public acceptance? The aim is to investigate patient and public preferences to generate information on acceptance and analyze the value of digital interventions. Preference evidence is a series of observable human behaviors that can be analyzed by the choices individuals make between alternative health states, health services, or health interventions. Choices define the value of attributes and alternatives in health care.

Acceptance is a requirement for active patient engagement and thus for efficiency (the greatest possible result with the least possible effort) and effectiveness (ability of the intervention to positively improve patients’ state of health in a targeted manner). To obtain information on acceptance, it is necessary to understand the trade-offs that patients make by weighing the advantages and disadvantages of therapy options using digital technologies. We also ask whether patients would accept a humanoid robot in neurorehabilitation. Our primary objective is to weight the criteria that impact patient and public acceptance. Secondary objectives include (1) a benefit-burden assessment (estimation of the maximum acceptable burden of technical features and therapy-related characteristics for the patient or individual, eg, no human contact), (2) overall comparison (assessment of the relative importance of attributes for comparing digital technologies), and (3) adherence (identification of key attributes that influence patient adherence). Our exploratory objectives include (1) heterogeneity assessment (how preferences differed based on participant characteristics) and (2) subgroup analysis (to explore and explain heterogeneity based on the correlation between therapy preferences and participants’ sociodemographic information, experience-based treatment history, and attitudes). Our methodological aims are to investigate the use of DCE and the impact on data quality, preferences, and choice consistency.

The following assumptions and hypotheses will be examined:

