**Preference elicitation or discrete choice experiment**
Dominance test: selection from a choice set with an openly dominant alternative (no copayment and 100% treatment success) to test the understanding of choice tasks and quality (validity)6 Choice tasks: choice best, choice second best, and dual response

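### Participants are told that each alternative is described by 7 attributes, but each task shows 4; inferences about the three hidden attributes could bias the weights and trade-offs

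*Protocol article*

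**What the plan says.** Two statements in the protocol article do not agree.

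- **What participants are told.** Survey Instrument Design says that in the introduction participants learn that "they will be presented with hypothetical therapy alternatives in various combinations and that each alternative is described by 7 attributes". Textbox 1 adds that all seven attributes and their levels are described and illustrated before the tasks begin.
- **What participants see.** Experimental Design says the preliminary findings "led to the decision to use a partial design (choice tasks include 4 of the 7 attributes"). Principal Findings confirms a partial profile. The stated reason is patient capacity: "The results of the preliminary study indicated lower attention and concentration abilities in the experimental group".

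Before the tasks, "participants will see a tutorial and exercises to answer the choice tasks" (Elicitation Format). The content of that tutorial is not reproduced. Textbox 1 lists "6 Choice tasks: choice best, choice second best, and dual response". The dual-response question is "Would you really choose the previously selected digital therapy in real life to improve your health" (Elicitation Tasks).

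The quantities at stake are also stated: "Our primary objective is to weight the criteria that impact patient and public acceptance" (Research Questions and Study Aim), and "the study objectives were to estimate the marginal rates of substitution and value equivalents for therapy attributes" (Elicitation Tasks).

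**The concern.** A respondent who has been taught seven attributes, and told that every alternative has all seven, can reasonably treat the three missing ones as present but unknown. They may then fill them in: direct contact with a professional probably costs more, or a dearer therapy probably works better. The model is fitted to the shown attributes only, so the value of such a guess is attributed to whichever shown attribute prompted it.

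The planned outputs are relative weights and rates of substitution, so a guess that loads onto copayment or success changes the figures to be reported. If patients and the general population guessed differently, part of that difference would look like a difference in preferences. The dual-response question is exposed too, since it asks for a real-life judgement on a therapy with three announced features unseen.

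The stated checks are not aimed at this. The pilot looked at signs, coefficients and estimation problems, and the indicators under Data Quality do not address inferred attributes. In the simulation below, coefficients keep their expected sign while their size is wrong.

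**Working it through.** **1. Text comparison.** Announced: 7 attributes per alternative. Shown: 4 per task. Hidden: 7 − 4 = 3, or 3/7 = 43%. The article gives no figure for inferred attributes, so there is none to reproduce.

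**2. How often a relevant attribute is hidden.** This assumes that attributes rotate evenly. The article states balance for levels, not for the appearance of attributes.

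- Possible sets of 4 from 7: C(7,4) = 35. Copayment and success appear together in C(5,2) = 10, so 10/35 = 28.6%.
- Given that contact is shown, there are C(6,3) = 20 sets, of which C(5,2) = 10 include copayment. Copayment is hidden in 1 − 10/20 = 0.5. The same holds for success, and for any other pair.
- Given that contact and copayment are both shown, there are C(5,2) = 10 sets, of which C(4,1) = 4 include success. Success is still hidden in 1 − 4/10 = 60%.

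**3. Mechanism.** To a first approximation,

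fitted coefficient ≈ true coefficient + P(other attribute hidden | this one shown) × inference slope × coefficient of the hidden attribute.

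Assume copayment −0.60, success 0.90 and contact 0.50, with attributes coded −1 to 1. The true success/copayment trade-off is 0.90/0.60 = 1.50, and contact/copayment is 0.50/0.60 = 0.83. If hidden success is inferred from shown copayment with slope 0.5, the copayment coefficient becomes −0.60 + 0.5 × 0.5 × 0.90 = −0.375. The success/copayment trade-off is then 0.90/0.375 = 2.40.

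**4. Simulation.** Conditional logit, 3 alternatives, 4 of 7 attributes shown at random, 60,000 tasks, one run per scenario. The other four coefficients were set at 0.3, 0.4, 0.4 and −0.3.

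| How hidden attributes are treated | Success/copayment (true 1.50) | Contact/copayment (true 0.83) |
|---|---|---|
| Equal across alternatives | 1.48 | 0.85 |
| Filled in at random, unrelated to shown levels | 1.55 | 0.83 |
| Success inferred from copayment, slope 0.25 | 1.90 | 1.05 |
| Success inferred from copayment, slope 0.5 | 2.48 | 1.36 |
| Success inferred from copayment and contact, slope 0.5 | 2.43 | 1.99 |

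Random fill-ins shrink the coefficients by about 7 to 15% but leave the ratios nearly intact. With slope 0.5 on copayment alone, the copayment coefficient falls in size from −0.60 to −0.36, and its share of total weight falls from 17.6% to 11.6%.

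**5. Direction.** Suppose direct rather than no contact is truly worth EUR 60 per month. If respondents assume that contact brings EUR 20 more copayment, the estimate is 60 − 0.5 × 20 = EUR 50. If they assume that it brings extra success worth EUR 20, the estimate is 60 + 0.5 × 20 = EUR 70. Both results follow directly from what was assumed, so neither sign nor size is established.

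**The case against.** The sentence in Survey Instrument Design is the article's summary of an introductory text, not the survey wording. The operative instructions are the tutorial, the exercises and the task screens, which are not reproduced. A line saying that features not shown are equal would sit there, and a condensed article would commonly leave it out. The team also tested full against partial designs, assessed clarity, and revised descriptions after pretesting and piloting. This stands: the article's silence does not show that respondents lack the instruction. It does not rescue the sentence itself, which misdescribes the tasks.

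A reader might also infer that a partial-profile analysis is invalid unless hidden attributes are taken as equal, or that the weights and euro trade-offs are already biased by a known amount. The documents support neither. Unrelated fill-ins leave the ratios nearly unchanged. Material bias in trade-offs needs guesses that track the shown levels and share a direction across respondents, and the documents give no evidence of that in either group. The coefficients, slopes and euro values above are all assumed.

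Finally, a full check that interacts every technical level with two display indicators would be heavy. Table 1 gives 4 + 4 + 2 + 4 + 3 = 17 level terms, hence 34 extra parameters with 6 tasks per person. That is a fair reason to keep the check small.

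**Conclusion.** The contradiction is real: participants are said to be told that seven attributes describe each alternative, while each task shows four. As described, the instruction is false for the tasks used and may lead respondents to infer the three hidden attributes. Where those inferences are related to the shown levels, they would be credited to the shown attributes and would bias the weights and trade-offs.

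The size and direction of any bias are unknown. The simulated range for the success/copayment trade-off, from 1.48 to 2.48 around a true 1.50, depends on assumed coefficients, assumed inference rules and even rotation of attributes. It shows that the mechanism can matter, not that it has operated. If the survey screens already tell respondents to treat hidden features as equal, only the article's description needs correcting.

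**What to change.** **Wording.** Reconcile Survey Instrument Design with Experimental Design. Unless the survey already says so, put a sentence such as the following in the introduction, the tutorial and the task screen: *Each therapy is shown on 4 of the 7 features; please treat the features that are not shown as identical in all three therapies.* This costs one sentence. It does not fully settle the real-life follow-up question, where the hidden levels still matter in absolute terms, so those answers should be interpreted with that in mind.

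**If the wording changes during data collection.** Recruitment began in January 2022. A change would split the data by instruction version, possibly unevenly between patients and the general population. Record the version each respondent saw and adjust for it.

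**For data already collected.** Run one small sensitivity analysis by either route:

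- Interact a key attribute with indicators for copayment shown and success shown. For contact this adds 2 level terms × 2 indicators = 4 parameters rather than 34.
- Re-estimate trade-offs from tasks that display the compensating attribute. Under even rotation, copayment appears in half of the tasks showing contact, so the standard error of the contact coefficient would rise by roughly √2 ≈ 1.4.

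Report either as a check with wider intervals. Neither removes the problem fully: in tasks showing contact and copayment, success would still be hidden in 60%.
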